### Usual care control group: family-based behavioral therapy (FBT) for pediatric weight loss

4.3

Families randomized to the usual care group will be referred to the tertiary care FBT weight control program offered at CHEAR. The tertiary care program is based on the gold-standard FBT for pediatric weight loss [[65], [66], [67], [68]] and includes the same nutrition and physical activity education as well as behavioral strategies delivered in GSH. However, families in FBT will attend 16-weekly, and then 4 bi-weekly group sessions over a 6-month period at our site in La Jolla. Group sessions are conducted separately for parents and children and last 60 min each week. Both parents and children will receive weekly age-appropriate manuals and activities to do at home. Families may continue to follow-up with their PCP (time frame to be determined by the PCP) to follow anthropometric changes.

### Treatment fidelity

4.4

Health coaches for the GSH intervention and parent and child group leaders in FBT are marriage and family therapy trainees or masters level students. The majority of the staff and health coaches were also bilingual and bicultural. All health coaches attended a one-day training with experts in the field of pediatric weight loss ([name], [name]). These trainings reviewed current information regarding nutrition, physical activity, and behavioral strategies for weight loss, and protocols for delivering FBT and GSH. Health coaches were given treatment manuals and protocols in order to maintain treatment fidelity and quality of care. Prior to the start of the intervention, health coaches shadowed a skilled health coach delivering the program to currently enrolled subjects. During the intervention, all sessions will be audiotaped and 10% of tapes will be reviewed during weekly supervision. During the intervention, health coaches have access to both investigators and research assistants via e-mail and phone should any emergent questions arise in the office.

## Data analysis

5

5.1. This study is a pragmatic randomized control trial using a one-to-one randomization ratio within each clinic, randomizing at the level of the individual. First, we will track the number of sessions each family attended within each group and examine if there is a difference in the proportion of sessions attended between groups using a generalized linear model (binomial family). For our second primary outcome, we will estimate between-group differences (GSH vs FBT) in BMI percentile/z-score (our second primary outcome) over 6- and 12-month assessments using linear mixed effects (LME) analysis adjusting for corresponding baseline BMI percentile/z-score values. BMI z-score is calculated using the formula: [(BMI/M)^L^ −1]/(L x S). (M = median; L = power in the Box-Cox transformation; S = generalized coefficient of variation; values vary based on age in months of the child) All models will adjust for standard patient characteristics (age, race/ethnicity, sex, insurance type) as planned covariates and any differential effects across clinics (i.e., main effect rather than random effect given limited number of clinics).

As a secondary analysis, we will assess the degree to which treatment assignment (GSH vs. FBT) was associated with change in proposed mediators (considered outcomes in these analyses) including child lifestyle behaviors (e.g., eating and physical activity behaviors), parent self-efficacy, parent empowerment, and parent support behaviors (e.g., parent monitoring, adherence to treatment recommendations) using LME models. For mediation modeling, we first will estimate the effect of allocation on a change in proposed mediators (path ‘a’) at 6-months with adjustment for corresponding baseline values. If significant, we will then add baseline and 6-month terms for mediators to the LME model examining their relationship to the primary outcome of BMI percentile/z-score. The indirect effect of group allocation on BMI percentile/z-score through changes in mediators (path ‘b’) will be computed using a product of coefficients method (path ‘a*b’) along with bootstrap confidence intervals. As an adjunct to the primary analyses, we will also explore attendance patterns using a cox proportional hazards regression model to examine predictors of attrition, defined as missing 3 or more consecutive sessions.

5.2. Cost-effectiveness analysis: The cost-effectiveness analysis (CEA) will follow well-established guidelines developed by Drummond et al. [69] and Haddix et al. [70] and include identification of all relevant costs and consequences for each of the interventions and alternatives, accurate measurement in appropriate effectiveness units, sound valuation, and sensitivity analysis to test uncertainties. The final outcome of the CEA in this study is the cost per BMI unit reduced, evaluating the incremental differences between cost and effectiveness in the GSH model and usual care. The precision of the incremental cost-effectiveness ratio (ICER) will be investigated through sensitivity analyses. To account for the non-parametric nature of the data, we will use bootstrap to create confidence intervals for the mean costs and effectiveness for the comparison. ICER will be developed using the nonparametric permutation. A scatter plot of 5000 bootstrapped ICER will be generated by drawing a random sample with replacement [71]. The CEA results will be presented in a cost-effectiveness acceptability curve. The uncertainty of the parameters will be explored in sensitivity analysis.

5.3. Power Analysis: For this trial, sample size estimates took attrition into account. Our first primary hypothesis is that a greater proportion of families in the intervention group will enter into and attend behavioral treatment for obesity. However, there was lack of evidence from previous studies to conduct a power analysis with this outcome. Therefore, power analyses were based on changes in BMI z-score (our second primary outcome) that was supported by observations in the GSH pilot which estimated a decrease in BMI z-score d = |1.71–1.50|/.30 = 0.667. Empirical power estimates were assessed by generating multivariate random samples that were matched to the expected BMI z-score for each condition and variability over time as observed in our pilot study. We expected decreases in BMI z-score of 0.10 among those enrolling in GSH, and a slight increase of 0.05 in BMI z-score in the usual care group. Each of 1000 simulated data sets was analyzed using a LME (random intercepts: patients within clinics) and specific output saved (e.g., standardized regression coefficients, p-values). The percentage of datasets with significant effects (i.e., p < 0.05) for the primary hypothesis comparing GSH vs. usual care provided a simulation-based estimate of power for the primary hypothesis. With a median between-group effect of −0.39 (s d. = 0.13) across 1000 data sets, the planned design would provide greater than 0.82 power for detecting the effect with allowance for up to 20% lost to follow up [72]. We allow up to 20% loss to follow-up to maintain the integrity of the sample for data analysis, and have been able to limit our loss to follow-up in previous trials to 13–18% of the sample. Given these parameters, we estimated that we would need to recruit 200 families into the trial, 100 in GSH and 100 in FBT. With a sample of 200 to support between-group comparisons of BMI percentile/z-score, we estimate we will have power >0.95 to detect a difference in the proportion of sessions attended in a generalized linear model (binomial) with two-sided alpha <0.05 given that we expect >85% attendance in GSH and 60% attendance in FBT. All analyses of primary outcomes will use an intention to treat sample with analyses of all participants who provided both baseline and post-treatment assessments.

5.4. Missing data: The default handling of missing data in mixed models is to make use of all available information from each participant (i.e., no data or cases are deleted) in estimating model parameters [73]. We plan to assess patterns of missing assessments, evaluate any predictors of missing assessments, and evaluate assumptions of methods for applying models to multiply impute data sets. Multiple imputation would be used in an effort to sustain power to compare treatment arms under conditions of data that is missing at random. This approach is both efficient and unbiased, provided that the missing data mechanism is ignorable, the model is correctly specified, and estimated using full likelihood procedures [73]. This approach is advocated as an optimal approach to handling missing data [74] and can help to reduce potential biases in the data.

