## Intervention

4

Parent-child dyads from each site will be randomly assigned to GSH delivered in the primary care setting or FBT delivered in an academic setting. Two large pediatric practices in San Diego County (specifically located in Chula Vista and Escondido, where rates of childhood OW/OB are 38% and 39% respectively) were recruited to participate in this study. Families randomized to GSH will attend 14 sessions (4 consecutive weekly meetings, and then 10 sessions every other week) spanning a 6-month period. Each session will be 20 min in length except for the first session which can last up to an hour, and both parent and child will attend these sessions. During the session, health coaches will answer any questions about healthy dietary and physical activity behaviors, assist parents with problem-solving, and promote accountability.

Families randomized to FBT will attend 16 weekly sessions and then 4 sessions every other week for a 6-month period. Each session lasts 60 min and are conducted in a group format where parents attend one group and children attend another group. Content of the child group mirrors that of the parent group except that information is delivered in a developmentally appropriate format for children. The same information is provided in both GSH and FBT and cover the core nutrition concepts, physical activity behaviors, and basic behavioral strategies that are effective in weight loss. Intervention topics are listed in Table 2. The overall goal of this program is to help children improve their weight status by losing ½ to 1 lb per week [12]. Parents interested in losing weight are also encouraged to do so since parent weight loss is highly correlated with child weight loss [44].

**Table 2 tbl2:** FBT vs. GSH session topics.

Week #	FBT Session #	FBT Topic	GSH Session #	GSH Topic
1	1	Introduction	1	Introduction
2	2	Dietary Changes	2	Dietary Changes
3	3	Stimulus Control/The Home Environment	3	Stimulus Control/The Home Environment
4	4	Physical Activity	4	Physical Activity
5	5	Problem Solving	–	–
6	6	Positive Parenting/The Rewards System	5	Motivation System and Parenting Skills
7	7	Lifestyle & Sedentary Behaviors	–	–
8	8	Problem Solving around High-Risk Situations	6	Team Building
9	9	Motivation	–	–
10	10	Team Building	7	Problem Solving
11	11	Review	–	–
12	12	Behavior Chains	8	Behavior Chains
13	13	Body Image & Teasing	–	–
14	14	Tricky Hunger & Emotional Eating	9	Emotional Eating
15	15	Shopping on a Budget	–	–

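### The binomial GLM named for the attendance primary outcome has no term for correlation among one family's 14 or 20 sessions, so its model-based standard error cannot be relied on

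*Protocol article*

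**What the plan says.** The protocol article names attendance as its first primary outcome. Section 5.1 describes the data as one count per family ("we will track the number of sessions each family attended within each group"), and says of the test that the analysts will "examine if there is a difference in the proportion of sessions attended between groups using a generalized linear model (binomial family"). Section 5.3 claims "power >0.95 to detect a difference in the proportion of sessions attended in a generalized linear model (binomial") at two-sided alpha 0.05, expecting more than 85% attendance in GSH and 60% in FBT.

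The number of sessions per family comes from section 4: "Families randomized to GSH will attend 14 sessions", and "Families randomized to FBT will attend 16 weekly sessions and then 4 sessions every other week", which makes 20. The randomised unit is the family, not the session: section 5.1 has a "one-to-one randomization ratio within each clinic, randomizing at the level of the individual", and section 5.3 plans to "recruit 200 families into the trial, 100 in GSH and 100 in FBT".

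Section 5.1 adds patient characteristics and a clinic main effect to all models. It assigns linear mixed-effects models to BMI. For attendance it names no device for repeated sessions within a family.

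**The concern.** A binomial GLM fitted to attended and missed counts has its dispersion fixed at 1. The 100 × 14 + 100 × 20 = 3,400 scheduled sessions then count as 3,400 independent observations, although only 200 families are randomised. Covariates and a clinic effect do not absorb the correlation among one family's sessions.

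The article itself points to such correlation. Section 5.1 defines attrition as a run of three or more consecutive missed sessions. Section 5.3 hypothesises a difference in entering treatment as well as attending it. The Introduction cites a study in which 63% of enrolled FBT families completed the programme.

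What is at stake is the p-value and confidence interval of a primary outcome. A small or absent difference could be declared significant, and the interval could be much too narrow.

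**Working it through.** **Inputs from the article:** 100 families per arm; 14 and 20 sessions; two-sided alpha 0.05; expected attendance 85% and 60%; up to 20% loss, so 80 per arm. **Assumed:** the ICC of attendance within a family, 0.05 to 0.50, because the article gives none.

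**1. The plan's own power figure.** Take the family as the unit (one yes/no per family, pooled variance under the null).
- 100 per arm: the null SE is √(2 × 0.725 × 0.275 / 100) = 0.0631 and the alternative SE is √(0.85 × 0.15/100 + 0.60 × 0.40/100) = 0.0606. Power = Φ[(0.25 − 1.96 × 0.0631)/0.0606] = 0.981.
- 80 per arm: 0.950.
- 1,400 against 2,000 independent sessions: 1.000.

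The stated figure therefore reproduces without assuming independent sessions.

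**2. Model fitted to counts.** The design effect is DE(m) = 1 + (m − 1) × ICC. With equal true attendance in both arms, the ratio of the true to the reported SE is

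k = √[(DE(14)/1400 + DE(20)/2000) / (1/1400 + 1/2000)],

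and the type I error is 2 × [1 − Φ(1.96/k)].

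| Assumed ICC | DE(14) | DE(20) | k | Type I error |
|---|---|---|---|---|
| 0 | 1.00 | 1.00 | 1.00 | 5.0% |
| 0.05 | 1.65 | 1.95 | 1.33 | 14.1% |
| 0.10 | 2.30 | 2.90 | 1.60 | 21.9% |
| 0.20 | 3.60 | 4.80 | 2.02 | 33.3% |
| 0.30 | 4.90 | 6.70 | 2.38 | 40.9% |
| 0.50 | 7.50 | 10.50 | 2.96 | 50.7% |

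Beta-binomial simulation (1,000 trials per setting, no true difference) agrees. At mean attendance 60% and 72.5%, rejection was 13.5% and 14.7% at ICC 0.05, 33.6% and 34.9% at ICC 0.20, and 50.3% and 49.8% at ICC 0.45.

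**3. Where the ICC might lie (illustration only).** Suppose 63% of families complete, as in the cited FBT study, the other 37% drop out at a uniformly distributed time, and active families attend 80% to 95% of sessions. The ICC is then 0.26 to 0.46. Using one session number (14 or 20) for both arms, the SE is 2.1 to 3.1 times too small and the type I error 35% to 53%.

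**4. Model fitted to one fraction per family.** The default variance is then that of a single yes/no per family, so the reported SE is too large by √[2 / (DE(14)/14 + DE(20)/20)].
- ICC 0.05: √[2/(0.118 + 0.098)] = 3.0.
- ICC 0.20: √[2/(0.257 + 0.240)] = 2.0.
- ICC 0.50: √[2/(0.536 + 0.525)] = 1.4.

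Simulated type I error was 0 to 0.3% for ICC 0.05 to 0.45.

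**5. After correction.** With family-level robust SEs, simulated type I error was 4.8% to 6.5% for ICC 0.05 to 0.45 (Monte Carlo SE √(0.05 × 0.95/1000) = 0.7 points). A quasi-binomial model with one common dispersion also works. At ICC 0.20 the dispersion is about (3.60 + 4.80)/2 = 4.2, and its SE relative to the true one is √[4.2 × (1/1400 + 1/2000) / (3.60/1400 + 4.80/2000)] = 1.01.

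Power at 85% against 60% with the correct SE is Φ(0.25/SE − 1.96), where SE² = 0.85 × 0.15 × DE(14)/(14n) + 0.60 × 0.40 × DE(20)/(20n). At ICC 0.50 it is 0.9999 (n = 100) and 0.999 (n = 80). With all-or-nothing attendance (ICC 1) it is 0.985 and 0.958.

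**The case against.** The strongest reply is that the article never says sessions are independent. It names a model family, records data per family, and condenses a fuller plan that may specify a robust or overdispersed variance. One fraction per family also fits the wording and does not inflate the type I error. The power claim reproduces with the family as unit. At the expected 85% against 60%, a correct standard error would almost always lead to the same decision.

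Much of this stands. A reader might infer that the plan declares the sessions independent, or that its test has a known error rate. The text supports neither: independence follows only from one way of fitting the named model, and the size depends on an ICC that the article does not give. The calculation also omits the planned covariates and assumes that all 100 families per arm are analysed.

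The reply does not rescue the specification. On counts the default standard error is too small, and on fractions it is too large, so neither reading of the unqualified model gives a valid one. The model is also a stated choice for a primary outcome, named twice, and not merely a detail left for later.

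A reader might also see an error in the unequal denominators, since 14 attended sessions are 14/14 = 100% in GSH and 14/20 = 70% in FBT. That follows from the declared outcome and from two packages of different length. It is not a fault in the analysis.

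**Conclusion.** The concern holds in conditional form. The model named for the first primary outcome does not account for correlation among a family's sessions. If it is fitted to counts with model-based standard errors, an ICC between 0.05 and 0.50 makes the standard error about 1.3 to 3.0 times too small and the type I error about 14% to 51%. A two-fold understatement and 33% belong to one point, ICC 0.20. If it is fitted to fractions, the test is conservative and the interval too wide.

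It would be wrong to conclude that the trial is underpowered for attendance. With all-or-nothing attendance per family, power is about 0.98 with 100 per arm and about 0.95 to 0.96 with 80, depending on the variance formula. The harm lies in the width of the interval and, near a null difference, in false positive findings.

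**What to change.** State in section 5.1, or confirm in the analysis plan, that the family is the unit of analysis for attendance. Keep the binomial GLM with family-level robust (sandwich) standard errors, or use a beta-binomial or quasi-binomial model. Report the marginal difference in proportion of sessions attended with its 95% CI.

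State also that every randomised family is included and that those who never attend count as 0. This needs saying because section 5.3 limits primary analyses to participants with both baseline and post-treatment assessments, whereas attendance can be counted for every randomised family.

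The cost is one line of specification. The sample size stays at 200. Compared with a default fit to counts, the interval will be wider, and correctly so. A sensitivity analysis on the 14 calendar weeks that Table 2 schedules in both arms (reading the row printed as week 10 between 19 and 21 as week 20) is optional and does not bear on the standard error.

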#### Measurements (Table 1)

3.6.1

Anthropometry (child and parent). Child and parent height will be measured using a portable Schorr height board (Schorr Inc, Olney, MD) in duplicate. Height will be recorded to the nearest 0.1 cm for both trials, and the average of the 2 values used for analysis. Body weight in kilograms will be measured in duplicate on a Tanita Digital Scale (model WB-110A). Body weight will be recorded to the nearest 0.1 kg and the average of the 2 values used for analysis. Height and weight will be converted to body mass index (BMI = [kg/m2]). Since children are growing, BMI will be translated to BMI for age percentile score using the CDC growth charts [35,36] and to standardized age and gender referenced BMI (BMI Z-scores) [37].

**Table 1 tbl1:** Schedule of assessments and measures.

	Measure	Baseline	Post-treatment	6-Month Follow-up
Anthropometry	Height/Weight	X	X	X
Demographics	Demographics and Medical History questions	X		
Parent assessments	Parent Importance, Confidence, & Readiness questionnaire [21] Lifestyle Behavior Checklist (Confidence scale) [23] Parent Resource Empowerment Scale [24] Activity Support Scale [25]	X X X X	X X X X	X X X X
Child Lifestyle Behaviors	Dietary History and Eating Behaviors Godin Leisure Time Exercise Questionnaire [41]	X X	X X	X X
Parent support & weight control behaviors	Frequency of self-monitoring behaviors		X	X
	Parent report of adherence to treatment recommendations		X	X
Enrollment/attendance, Treatment Adherence, Acceptability	Enrollment and Attendance (weekly assessment) Self-monitoring in habit books (weekly assessment) Acceptability		X X	X X X
Cost-effectiveness	Family utilization & cost data Administrative data	X X	X X	X X

Demographic Characteristics (baseline only). At the baseline assessment, parents will complete demographic questionnaires that include items on racial/ethnic identity, sex, income, education, marital status, health history, and medication use.

Parent Importance, Confidence, and Readiness for Change Questionnaire: This questionnaire is a self-report measure that assesses motivation for behavioral lifestyle change. It contains three subscales: importance of change, confidence to make changes, and readiness to change. In a weight control study for children age 7–13 years old and their parents, parental confidence predicted premature participant dropout, early treatment response (5-week child weight loss) and child weight loss at post-treatment [21].

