### Obesity management by the PCP prior to randomization

4.1

All clinics within the CPCMG network utilize the EPIC electronic health record (EHR) and have a basic obesity management tool for children. This tool includes: 1) alerts to physicians to address and document weight status in all children older than 2 years with OW/OB; 2) prompts to assess risk for obesity-related medical co-morbidities and relevant family history; 3) a tool to facilitate efficient assessment of parent readiness to make behavior changes; 4) a focused menu of options of strategies for weight loss; 5) alerts to obtain appropriate labs, schedule follow-up visits, and make sub-specialty referrals when necessary; and 6) links to handouts and referrals to weight loss treatment options at the tertiary care center. To determine whether parents are ready to engage in obesity treatment, the PCP (prompted by the EHR) will ask parents of all identified children 3 motivation questions: “On a scale of 1–5 with 1 being ‘not important’ and 5 being ‘very important’, how important is it for you to make changes to help your child lose weight at this time?”; “On a scale of 1–5 with 1 being ‘not confident’ and 5 being ‘very confident’, how confident are you that you can help your child lose weight at this time?”; and “On a scale of 1–5 with 1 being ‘not motivated at all’ and 5 being ‘very motivated’, how motivated are you to help your child lose weight at this time?”. These questions are based on the transtheoretical model of behavior change [45], and patients who report higher scores on these questions have reported greater success in weight loss activities [21,46,47]. Parents who report a 3 or higher on any question will be told about the study and asked if their name and contact information can be sent to the study coordinator. If the parent agrees, referrals to the study coordinator will occur via a link in the EHR and/or in person (if she is in the office that day). The study coordinator will contact the family and screen for eligibility. Once families have completed the consent process and baseline assessments, they will be randomized to the intervention (GSH) or usual care (FBT) group. Randomization will be conducted with a random number generator independent of the investigators and physicians. Participants will be informed of both intervention possibilities to ensure their commitment to both. Due to the clear differences in treatment groups, participants will not be blinded to the treatment arms.

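### The fixed covariate list leaves out baseline parental confidence, which the protocol itself cites as predicting dropout and child weight loss; adding it is a nearly free, modest improvement

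*Protocol article*

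**What the plan says.** Section 5.1 (Data analysis) sets the covariates for every model: "All models will adjust for standard patient characteristics (age, race/ethnicity, sex, insurance type) as planned covariates". Clinic enters as a main effect. The BMI mixed model also conditions on the starting value, "adjusting for corresponding baseline BMI percentile/z-score values". Parental confidence is not on the list. Baseline terms for proposed mediators enter the BMI model only in the secondary mediation analysis, and only if the effect of allocation on the mediator is significant.

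Section 3.6.1 describes the parent questionnaire on importance, confidence and readiness. It reports that in a weight-control study of children aged 7 to 13 "parental confidence predicted premature participant dropout, early treatment response (5-week child weight loss) and child weight loss at post-treatment". Table 1 schedules this questionnaire at baseline and at both later visits.

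Section 4.1 gives the order of events: "Once families have completed the consent process and baseline assessments, they will be randomized". The same section describes three short screening items on importance, confidence and motivation, and says that "patients who report higher scores on these questions have reported greater success in weight loss activities".

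Section 5.3 limits the primary analyses to participants with both a baseline and a post-treatment assessment. Section 5.4 plans to look for predictors of missing assessments and considers multiple imputation, but names no variables for the imputation model.

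**The concern.** The protocol has in hand, before randomisation and for essentially every randomised family, a score that it cites as related both to outcome and to dropout. Its fixed covariate list does not use that score. Two things are at stake.

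1. **Precision of the BMI comparison.** In a linear model, a baseline covariate that explains residual outcome variance reduces the standard error of the GSH–FBT difference.
2. **Credibility of the missing-data assumption.** A family without a post-treatment BMI adds little or nothing to the estimated contrast. The analysis then relies on dropout being ignorable given the covariates in the model, and the cited predictor of dropout is not among them.

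The covariate list is stated for all models rather than deferred, so it can fairly be compared with the protocol's own evidence.

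**Working it through.** **Inputs from the protocol (section 5.3).** 200 families, 100 per arm; up to 20% loss, so 80 per arm; power above 0.82 for BMI z-score; "With a median between-group effect of −0.39 (s d. = 0.13) across 1000 data sets"; significance at 0.05, taken here as two-sided.

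**Inputs that are assumed.** The share of BMI outcome variance that confidence explains beyond the planned covariates (R²), and the slope of dropout on confidence in each arm. The protocol gives neither.

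**Step 1. The plan's own power.** A two-sample normal calculation with d = 0.39 gives 0.694 (80 per arm) or 0.787 (100 per arm). Reading 0.13 as the standard error gives Φ(0.39/0.13 − 1.96) = Φ(1.04) = 0.851. Averaging two visits with 80 per arm gives 0.838 (correlation 0.4) or 0.813 (correlation 0.5). These values bracket 0.82. The simulation's variance and correlation inputs are not stated, so 0.82 can be neither confirmed nor called wrong. It is used below as the starting point.

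**Step 2. Precision gain in the BMI model.** At power 0.82 the standardised effect is 1.960 + 0.915 = 2.875. Adding confidence multiplies the residual SD by √(1 − R²), so power = Φ(2.875/√(1 − R²) − 1.960). The equivalent gain in families is 1/(1 − R²) − 1.

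| Assumed R² | Fall in SE | Equivalent extra families | Power |
|---|---|---|---|
| 0.01 | 0.5% | 1% | 0.824 |
| 0.02 | 1.0% | 2% | 0.828 |
| 0.05 | 2.5% | 5% | 0.839 |
| 0.10 | 5.1% | 11% | 0.858 |

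**Step 3. Bias from dropout.** Let confidence be standardised, let higher confidence go with better BMI change, and let 20% be lost in each arm with log-odds linear in confidence. Without confidence in the model, the bias in SD units is √R² × (mean confidence of retained FBT families − mean confidence of retained GSH families).

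- Same slope and same retention in both arms: the two means are equal and the bias is 0.
- Slope in FBT only, 0.7 per SD: retained FBT families average 0.130 SD above the randomised mean. Bias = √0.02 × 0.130 = 0.018 up to √0.10 × 0.130 = 0.041.
- Slope in FBT only, 1.1 per SD: the mean is 0.186. Bias = √0.02 × 0.186 = 0.026 up to √0.10 × 0.186 = 0.059.

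The one-arm range is therefore about 0.02 to 0.06 SD against a planned effect of 0.39 SD. In this set-up it pulls the contrast towards no difference. A large simulation gave the same range without confidence in the model, and about zero with it.

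**Step 4. Attendance model.** This is a binomial model and the link is not stated. Under a logit link, adding a prognostic covariate changes the coefficient to a conditional one and usually raises its standard error. A simulation with one yes/no outcome per family, 100 per arm, about 60% in the control arm and an assumed slope of 0.5 per SD gave mean standard errors of 0.364 unadjusted and 0.376 adjusted. Power may still rise because the coefficient moves further from zero. Planned power for this outcome is already above 0.95.

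**The case against.** The strongest reply is that the planned set is valid as it stands. Randomisation is individual, baseline BMI is already in the model, and leaving out one prognostic score does not bias a randomised comparison. That stands, and it makes this an improvement rather than the correction of an error.

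The reply also has force on size. The protocol gives no correlation, and what counts is the residual correlation after baseline BMI and demographics. The referral rule, "Parents who report a 3 or higher on any question will be told about the study", may narrow the range of confidence among enrolled families. The dropout in the cited study may mean leaving treatment rather than missing an assessment. Section 3.4 pursues missed assessments with payment, repeated rescheduling and transport.

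Sections 5.1 and 5.4 would also examine predictors of attrition and of missing assessments, and nothing prevents confidence from being used in imputation. This answers the point only in part, because neither section commits to it.

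A reader might infer three stronger claims that the documents do not support:

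- *That precision and robustness are thrown away.* The plausible precision gain is small, and robustness is weakened rather than lost.
- *That the BMI effect is biased by a material share of the planned difference.* This needs confidence to drive dropout differently by arm. The heavier FBT schedule and the expected attendance gap (above 85% against 60%) make that conceivable, but attendance is not assessment retention, and nothing in the protocol shows it.
- *That confidence is the only cited predictor.* Section 4.1 also credits the importance and motivation items with weight-loss success. Confidence stands alone only as a cited predictor of dropout and child weight loss together.

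**Conclusion.** The point holds as a modest, low-cost improvement. The covariate list in section 5.1 omits a score that is measured before randomisation and that section 3.6.1 cites as predicting both dropout and post-treatment child weight loss. Nothing elsewhere commits to using it in the primary models or in imputation.

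For BMI z-score, an additional R² of 0.01 to 0.10 would lift power from 0.82 by about 0.4 to 4 percentage points. Protection against dropout bias ranges from nothing (equal slopes and similar retention) to about 0.02 to 0.06 SD (dropout driven by confidence in one arm, 20% loss per arm). Both ranges rest on assumed inputs. For attendance, no reduction in standard error should be claimed under a logit link. The primary analysis remains valid if the change is not made.

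**What to change.** In section 5.1, add the baseline confidence subscale of the parent questionnaire, as a continuous score, to the planned covariates of the BMI z-score mixed model. In section 5.4, name it as a variable in any imputation model. Leave the other covariates as they are.

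It may also be added to the attendance model. If so, state the link function and say that under a logit link the treatment estimate becomes conditional on confidence.

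Fix this before outcome data are seen, since a covariate added later is open to challenge. The cost is a line or two of text and about one degree of freedom. The score is already collected before randomisation, so no new data are needed and adjusting for it brings in no post-treatment variable.
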